#### Secondary hypotheses

2)Kava will be superior to placebo on a range of secondary affective disorder outcome scales (Beck Anxiety Inventory [39], Penn State Worry Questionnaire [40]*,* and Montgomery–Åsberg Depression Rating Scale [41]).3)Kava will be superior to placebo on health-related quality of life measured using The World Health Organization Quality of Life - BREF (WHOQOL-BREF) [42], the Social Re-adjustment Rating Scale [43], and the Kessler Psychological Distress Scale [44].4)Overall sexual satisfaction and performance rated on the Arizona Sexual Experiences Scale [45] will be in favour of kava compared to placebo, in women but not men.5)Personality trait factors including anxiety, extraversion, socialization, and aggression rated on the Swedish Universities Scales of Personalities (SSP) may be associated with GAD symptomatology and will be measured via this self-reporting measure.6)Anterior cingulate cortex (ACC) activation and metabolite profiles will be differentially affected in the kava treatment group over placebo from baseline to week 8. Specifically, for ACC metabolite levels, there will be an increase in GABA and decrease in glutamate/glutamine ratio (Glu/Gln); ACC activation: reduction in activation during resting state; ACC activation: reduction in activation associated with anticipatory anxiety in a task-dependent manner. Further, individual differences in rostral ACC activation measured pre-treatment may predict GAD treatment outcomes for kava compared to placebo. Increased levels of activity in the ACC will also be associated with better clinical outcome in GAD participants.7)Response to kava will be moderated by GABA transporter polymorphisms. Specifically, for every rs2601126-T allele or rs2697153-A allele an individual carries, the greater the reduction of anxiety that will be observed.8)Individuals in the kava group will have distinct gene expression change profiles compared to the placebo group. Specifically, we hypothesise that expression of GABA pathway genes will be up-regulated following kava treatment and remain stable in the placebo group.

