**Fig. 3 Fig3:**
[figure not shown]
Clinical trial flowchart

Participants will be required to attend seven visits at the study sites at week 0 (baseline), 2, 4, 8, 12, 16, and 18. At the baseline visit, participants will complete informed consent forms, screening assessments, and mood and anxiety questionnaires (self-reporting and interview-based). Brain imaging component visits (Melbourne site only) are to be scheduled within one week of baseline and week 8 visits.

The study employs an additional two-week single-blind placebo-controlled post-study observation period (that is, for a total trial length of 18 weeks - refer Fig. 3).

All eligible participants will be randomly allocated to a treatment arm, and corresponding treatment will be provided following clearance of blood tests taken at the baseline visit. All subsequent visits will follow the same outline of the baseline session excluding consent forms and screening assessments and including a safety assessment. In addition, participants will be required to provide a blood sample within several days of the baseline, and at week 2, 8, and 16 visits. For female participants not taking hormone-modulating contraception who are otherwise eligible to partake in the brain imaging components, the baseline visit is to be scheduled on days 1–5 of the menstrual cycle.

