### Secondary outcome measures

In addition, the Beck Anxiety Inventory (BAI) will be used as a participant self-report scale to assess anxiety levels. It consists of 21 items ranging from 0 (not present) to 3 (severe). These items are more somatically orientated than the SIGH-A and provide additional information on anxiety outcomes.The Penn State Worry Questionnaire (PSWQ) is a 16-item self-report measure of the intensity and excessiveness of worry. Examples of items are “Many situations make me worry” and “Once I start worrying, I cannot stop.” Participants rate items on a 5-point Likert scale from 1 (“Not at all typical of me”) to 5 (“Very typical of me”). Total scores range from 16 to 80, with higher scores indicating pathological worry. The PSWQ is widely used and has shown good to very good internal consistency, test-retest reliability, and discriminant validity for GAD versus other anxiety disorders [49].Mood will be assessed at each visit using the SIGMA (Structured Interview Guide for the Montgomery–Åsberg Depression Rating Scale (MADRS)), a diagnostic questionnaire which measures severity of depression symptoms. The SIGMA provides structured questions for each item to ensure standardisation of administration. Each item yields a score of 0 to 6, producing an overall score ranging between 0–60. A higher MADRS score indicates more severe depression. Inter-rater reliability with the SIGMA is reported to be excellent (*r* = 0.93) [50]. The use of this scale is important, as sufferers of GAD often have co-morbid depression, which may affect their response to treatment.Quality of life/life stressor measures will be administered at selected visits. The WHOQOL-BREF measure is a reduced version of the original instrument, designed for clinical trial use. It comprises 26 items, covering the domains of physical health, psychological health, social relationships, and environment. The Social Readjustment Rating Scale (SRRS) is a scale using ‘Life Change Units’ (LCUs) to quantify the number and severity of life stressors occurring in the preceding 12-month period. Both will be administered at baseline and at week 16. The Kessler Psychological Distress Scale (K10) is a 10-item questionnaire designed to obtain a global measure of perceived stress level, with questions pertaining to anxiety and depressive symptoms experienced in the past four-week period. For this study it will be administered at each visit.The Arizona Sexual Experiences Scale (ASEX) will be employed to assess the effects of kava on participants’ sexual functioning. Specifically, the self-report scale explores effects on desire, arousal level, and physiological responses over the course of the past week. It consists of five self-report items, each rated on a 6-point scale. Total scores can range between 5–30, where higher scores indicate greater sexual dysfunction. The use of this scale is important, as conventional SSRI antidepressant treatments (used to treat GAD) commonly cause sexual side effects, and results of a previous study [37] showed a significant improvement in sex drive for women. If this finding is replicated, it will show a point of difference between kava and conventional treatments. Due to the sensitive nature of the items, completion of this scale is optional.The Swedish Universities Scales of Personalities (SSP) is a 91-item self-rated questionnaire based on the Karolinska Scales of Personality (KSP), a scale designed to measure stable personality traits related to psychopathology [51]. It assesses four general temperament dimensions: anxiety, extraversion, socialization, and aggression. This questionnaire will be given to participants after their initial baseline visit to complete in their own time and return at the next visit.Genotyping of candidate and haplotype-tagging single nucleotide polymorphisms in monoamine, glutaminergic, and GABA transporter genes, measured via blood sample at week 1, will be achieved using a Sequenom Mass-Array.A custom RT^2^ PCR Array (Qiagen) will be used to examine gene expression of candidate genes (Table 1) at weeks 1 and 8.

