GRIK5	Glutamate receptor, ionotropic, kainate 5
GRIN1	Glutamate receptor, ionotropic, N-methyl D-aspartate 1
GRIN2A	Glutamate receptor, ionotropic, N-methyl D-aspartate 2A
GRIN2B	Glutamate receptor, ionotropic, N-methyl D-aspartate 2B
GRIN2C	Glutamate receptor, ionotropic, N-methyl D-aspartate 2C
GRM1	Glutamate receptor, metabotropic 1
GRM2	Glutamate receptor, metabotropic 2
GRM3	Glutamate receptor, metabotropic 3
GRM4	Glutamate receptor, metabotropic 4
GRM5	Glutamate receptor, metabotropic 5
GRM6	Glutamate receptor, metabotropic 6
GRM7	Glutamate receptor, metabotropic 7
GRM8	Glutamate receptor, metabotropic 8
ADRA1A	Adrenoceptor alpha 1A
ADRA1D	Adrenoceptor alpha 1D
ADRA2A	Adrenoceptor alpha 2A
ADRB2	Adrenoceptor beta 2
ADRB3	Adrenoceptor beta 3
SLC18A2	Vesicular monoamine transporter
SLC6A2	Norepinephrine transporter
CYP3A4	Cytochrome P450 3A4
CYP2D6	Cytochrome P450 2D6
CYP2E1	Cytochrome P450 2E1
AR	Androgen receptor
NRG1	Neuregulin-1
BDNF	Brain-derived neurotrophic factor
ABCG2	Breast cancer resistance protein
ABCB1	P-glycoprotein
GAPDH	Reference genes
SADH	Reference genes
B2M	Reference genesAnterior cingulate cortical (ACC) region metabolite profiles, including N-acetyl-l-aspartate (NAA), creatine (Crn), glutamate/glutamine (Glu/Gln), and gamma-amino butyric acid (GABA), will be measured using single voxel magnetic resonance spectroscopy (MRS) at weeks 1 and 8.ACC region activity at rest and functional connectivity network (that is, default mode network) will be analysed using resting-state functional magnetic resonance imaging (fMRI) at weeks 1 and 8.ACC region task-dependent activation levels associated with anticipatory anxiety will be assessed using task fMRI (the International Affective Picture System (IAPS; [52]) at weeks 1 and 8.Acute anxiety levels related to undergoing scanner session at weeks 1 and 8 will be measured on the Spielberger State-Trait Anxiety Inventory — Trait and State components [53].

Inclusion criteria*Aged between 18–70 yearsMeets the DSM-IV and DSM-5 diagnostic criteria for generalised anxiety disorder (GAD) based on structured interview; Mini International Neuropsychiatric Interview-6.0 (MINI 6.0) [54], (note that while the MINI 6.0 uses the DSM-IV criteria, the same criteria are used in the DSM-5)Presents with anxiety (SIGH-A ≥ 18) at the time of study entryFluent in spoken and written EnglishProvides a signed copy of the consent form

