### Power analysis

The study will recruit a sample size of 210 participants (105 participants per arm). The study is powered to detect a small-to-moderate difference between active treatment and placebo on efficacy outcomes. Data will be analysed using data with at least one post-baseline, and all data including baseline measurement, in an intention-to-treat analysis. As such, a conservative effect size F of 0.15 on the primary outcome measure (SIGH-A) for a two-tailed analysis (with alpha = 0.05), and the study powered at 80 % (Z beta = 0.80), with a correlation among repeated measures (analysis of variance (ANOVA) model) over six time points, will require 206 participants (critical F of 3.88). A sample size of 206 (rounded up to 210) will be sufficiently powered to provide a statistical difference between active treatment and placebo groups (using the intention-to-treat analysis) with the data.

The sample size of the imaging component of this study is 40 per treatment arm (*n* = 80). Following 12-week supplement administration, a recent MRS study with a sample size of 24 (12 in each arm) detected significant changes in metabolites by 39 % [60]. Our sample size of 40 participants in each arm will provide higher statistical power compared to previous studies, whilst still maintaining sufficient power with a 10 % participant attrition rate, as well as attrition due to unreliable metabolite estimates in one or both time points.

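### The single take-home personality questionnaire (SSP) may be completed before or after the first dose, so the trait scores for hypothesis 5 can mix pre-dose and on-treatment answers

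*Protocol article*

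**What the plan says.** Under Secondary outcome measures, the article describes the SSP as a 91-item self-rated questionnaire with four dimensions: anxiety, extraversion, socialization and aggression. It derives from "a scale designed to measure stable personality traits related to psychopathology". On timing it says: "This questionnaire will be given to participants after their initial baseline visit to complete in their own time and return at the next visit". No other SSP administration is described.

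Under Secondary hypotheses, hypothesis 5 says that these trait factors "may be associated with GAD symptomatology and will be measured via this self-reporting measure".

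Under Study design and plan, participants attend "seven visits at the study sites at week 0 (baseline), 2, 4, 8, 12, 16, and 18". The same section says that "corresponding treatment will be provided following clearance of blood tests taken at the baseline visit", and that "participants will be required to provide a blood sample within several days of the baseline, and at week 2, 8, and 16 visits". It also places the first imaging attendance, at Melbourne only, within one week of baseline.

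**The concern.** The SSP is meant to characterise participants by enduring traits, and such a measure is best taken before treatment can influence it. Here the form goes home and may be filled in at any time until the next visit, while treatment begins within that period. One of the four dimensions is self-rated anxiety, which lies close to what kava is expected to improve.

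At stake is the interpretation of hypothesis 5, which does not say at which visit GAD symptoms are to be related to the traits.

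- If they are baseline symptoms, a form completed on treatment pairs a later self-rating with an earlier symptom score.
- If they are post-baseline symptoms, both the SSP anxiety score and the SIGH-A could carry an early effect of treatment, and that shared influence could differ between arms.

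In either case, pre-dose and on-treatment answers would be pooled as if they were the same measurement.

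**Working it through.** The plan gives no figure on this point, so the check sets the timing statements side by side.

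1. **Window opens.** The form is handed out after the baseline visit, which the schedule labels week 0 (Secondary outcome measures; Study design and plan).
2. **Window closes.** The form is returned at the next visit. In the list of seven visits this is week 2, so the window is up to 2 × 7 = 14 days. Only the return is tied to that visit; completion may come on any earlier day.
3. **Treatment starts inside the window.** Supply follows clearance of the baseline blood tests, and the sample is taken within several days of baseline. The article gives no day for the first dose. Two other statements imply that it comes before week 2: treatment lasts 16 weeks with an end-of-treatment visit at week 16 (Treatment interventions, randomisation, and blinding; Primary hypothesis), and liver function during the study is first checked at week 2 (Monitoring and treatment compliance).
4. **Range of exposure at completion.** From steps 1 to 3, a participant who completes the form before blood clearance has 0 days of treatment. One who completes it just before the week 2 visit has had somewhat less than 14 days, counting weeks from the baseline visit. The document gives no distribution of completion days, so the share of forms completed on treatment cannot be calculated.
5. **Imaging participants.** Up to 80 of the 210 participants (80/210 = 38%) have a scan within one week of baseline, and hypothesis 6 treats the first scan as pre-treatment. If that attendance counts as the next visit, their forms could come back before any dose. The article does not say whether it counts. The remaining 210 − 80 = 130 have no listed attendance between baseline and week 2.
6. **Could the anxiety score move in under two weeks?** The scale is described as measuring stable traits, which argues against a large shift. However, Background evidence reports an earlier three-week crossover trial in which HAM-A fell by 9.9 points in the first kava phase and by 0.8 in the first placebo phase. If the three weeks cover the whole crossover, each phase was shorter than that. This shows that rated anxiety symptoms can change quickly on kava. It does not show that the SSP anxiety score would change, or by how much.
7. **Is there a substitute?** The article also says: "Acute anxiety levels related to undergoing scanner session at weeks 1 and 8 will be measured on the Spielberger State-Trait Anxiety Inventory". That measure includes a trait component, but it is tied to the scanner sessions and so to the imaging subset. It does not cover extraversion, socialization or aggression.

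**The case against.** The strongest reply has four parts.

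- **Completion is not placed after treatment start.** A reader might infer that every SSP is an on-treatment measurement because it is returned at week 2. The text does not support this. Every participant has some days between the baseline visit and blood clearance, and imaging participants may return the form earlier. This part stands: on-treatment completion is possible but not built in.
- **The use is narrow.** A reader might infer that the SSP will serve as a predictor or moderator of response to kava, so that its timing would bias a treatment finding. Hypothesis 5 states only an association with symptoms. Hypotheses 6 and 7 name a predictor and moderators of response, and the SSP is not among them. This stands and limits what is at stake.
- **Early dropouts.** A reader might add that those who leave before week 2 return no form. The Power analysis section already restricts the analysis: "Data will be analysed using data with at least one post-baseline". The earliest scheduled post-baseline measurement is week 2, so these participants are outside the stated set anyway. At most, an association with baseline symptoms loses some cases. This is not a separate fault.
- **The article is condensed.** Instructions for a take-home form, and a field for its completion date, may sit in the full protocol or case report form. That is fair for the date, whose absence here proves nothing. It does not dispose of the point, because the article states the procedure, and that procedure leaves completion open across the start of treatment.

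The stable-trait description also carries weight, but it bears on how large an effect could be and does not rule one out for a self-rated anxiety dimension.

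**Conclusion.** The point holds as a minor timing weakness. As written, the only described SSP administration allows completion on either side of the first dose, so the trait scores used for hypothesis 5 may mix pre-dose and on-treatment answers. Exposure at completion can run from none to just under two weeks. Neither the proportion of forms affected nor the effect on the scores can be sized from the document, and any percentage would rest on assumed start days and completion patterns that have no basis in the text.

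The conclusion assumes that the next visit means week 2 for participants without an early scan, and that blood clearance and first dose fall before week 2, as the schedule implies. The primary SIGH-A analysis, the sample size and the stated kava-placebo comparisons do not use the SSP and are unaffected.

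**What to change.** Change the SSP text under Secondary outcome measures so that the questionnaire is completed and dated before the first dose, either at the baseline visit or at home before the first tablet is taken. The wait for blood clearance already provides a pre-dose interval for this. For hypothesis 5, flag any form dated after the first dose, or exclude such forms in a sensitivity analysis.

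The cost is a slightly longer baseline visit for a 91-item form, or one reminder before treatment is started. The change is best made before enrolment, which the article gives as still to begin, because a pre-treatment score cannot be recovered once dosing has started.

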### Treatment interventions, randomisation, and blinding

The active treatment (kava) and placebo product will be identical in colour, size, and shape, bottled and labelled with trial treatment numbers by an independent researcher. The kava is a high-quality noble *Borogu* cultivar acquired from Southern Pentecost Island, Vanuatu, and manufactured by MediHerb (Integria Healthcare (Australia) Pty. Ltd.). Each tablet is standardised to contain 60 mg of kavalactones with a higher level of kavain and dihydrokavain, and a lower relative level of dihydromethysticin. To ensure replication of odour, a small porous sachet of kava powder is inserted into all treatment bottles. The trial products will be manufactured and stored in accordance with manufacturer instructions, following Pharmaceutical Good Manufacturing Practice.

Participants are assigned study identification numbers sequentially, and treatments are randomised via identification numbers using permutated 3×2 block randomisation, for example, ABAAABABBBA, based on these numbers. Randomisation is performed by staff unrelated to the study. Treatment is allocated sequentially to enrolled participants by trial clinicians who are blinded to treatment coding (with no identifying details on the bottle of which group [A or B] each participant is assigned to, thus providing double-blinding). Participants will take two kava tablets twice per day (total of 240 mg of kavalactones per day) or matching placebo for 16 weeks.

### Statistical analyses

Analysis of data will be conducted with blinding to group allocations. The primary efficacy analysis will assess average treatment group differences for the primary outcome measure (SIGH-A) over the entire study period using a likelihood based mixed-effects model, repeated measures approach (MMRM). Results from the analysis of dichotomous data (for example, demographics and genetic data) will be presented as proportions (for example, relative risks), with 95 % confidence interval, and Fisher’s exact test *P* value where appropriate. Non-parametric statistics will be used when assumptions for parametric methods are violated. Cohen’s *d* effect sizes will be calculated. All tests of treatment effects will be conducted using a two-sided alpha level of 0.05 and 95 % confidence intervals. Data will be analysed using Statistical Package for Social Sciences software (SPSS) [55].

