### Hypotheses

#### Primary hypothesis

Kava will be superior to placebo in the treatment of GAD symptoms, assessed by change in Structured Interview Guide for the Hamilton Anxiety Rating Scale (SIGH-A) [38] scores after the 16-week treatment phase.

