### Primary outcome measure

The primary outcome is symptoms of GAD measured by the Structured Interview Guide for the Hamilton Anxiety Rating Scale (SIGH-A), at baseline and subsequent visits up to 18 weeks following randomization. The SIGH-A is a widely used measure of anxious symptomatology in GAD research. It includes measures of persistent worry, anxiety, mood, and somatic symptoms. The SIGH-A has been used in previous studies of pharmacological and psychological treatments for people with GAD. It is reliable (intraclass correlation coefficients for inter-rater reliability of 0.98 and test-retest reliability of 0.88), has high convergent validity with structured clinical ratings of symptoms of GAD (for example, MINI PLUS 6.0 [46]), and is sensitive to change [47, 48].

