### Monitoring and treatment compliance

Study staff involved in all aspects of participant recruitment, assessment, and monitoring hold postgraduate psychology qualifications, undergo training including inter-rater reliability of interviewer scale measures, and are supervised by psychiatrists and medical staff. This study has comprehensive medical supervision. Regardless, the occurrence of an adverse event (AE) may come to the attention of study personnel during study visits and interviews of a study subject presenting for medical care, or upon review of subject data by a study monitor. Any medical condition that is present at the time that the subject is screened for inclusion will not be reported as an AE. However, if it deteriorates at any time during the study, it will be recorded as an AE. All AEs will be graded for severity and relationship to study product. Participants will also be required to complete the Systematic Assessment for Treatment of Emergent Effects (SAFTEE) [65] at each assessment session to assess for AEs. All AEs will be recorded in the adverse event log in the participant case report form (CRF), including the seriousness, severity, and relationship to study product, duration, and outcome. In all cases, researchers will maintain contact with participants who experience an AE until it has been resolved and symptoms disappear. They will also be asked to notify their general practitioner. If a worsening of a participant’s mental state occurs, the study psychiatrist and/or clinical psychologist will be consulted and appropriate steps taken.

Liver function will be assessed pre-treatment, and participants with any abnormal results will be excluded as a safety precaution. In people with healthy liver function, it is not expected that any elevation of serum liver enzyme levels will occur (based on our previous studies using similar standardised pharmaceutical-grade extract of kava). Nevertheless, liver function will be closely monitored via blood samples at regular intervals throughout the study (weeks 2, 8, and 16).

Participants will be required to take the tablets as instructed during the 18 weeks of the study. At each assessment session they will be asked to return all unused tablets, which will be counted for compliance rate (tablet counts will be employed by an independent researcher).

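### The primary analysis averages SIGH-A over the entire study period, which as written can include the off-treatment week-18 visit, while the primary hypothesis concerns change after 16 weeks of treatment

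*Protocol article*

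**What the plan says.** All references are to the protocol article.

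- **Primary hypothesis:** superiority of kava is judged by change in SIGH-A "scores after the 16-week treatment phase".
- **Statistical analyses:** "The primary efficacy analysis will assess average treatment group differences for the primary outcome measure (SIGH-A) over the entire study period", by MMRM.
- **Primary outcome measure:** SIGH-A is taken "at baseline and subsequent visits up to 18 weeks following randomization".
- **Study design and plan (text after Fig. 3):** there are "seven visits at the study sites at week 0 (baseline), 2, 4, 8, 12, 16, and 18". The design adds "an additional two-week single-blind placebo-controlled post-study observation period", and the same sentence counts it in an 18-week trial length.
- **Treatment interventions, randomisation, and blinding:** participants take kava "or matching placebo for 16 weeks".
- **Monitoring and treatment compliance:** "Participants will be required to take the tablets as instructed during the 18 weeks of the study".
- **Power analysis:** f = 0.15, two-sided alpha 0.05, 80% power and six time points give 206 participants (critical F 3.88), rounded up to 210. Neither the correlation nor the identity of the six time points is given.

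**The concern.** The hypothesis and the primary analysis name different quantities. One is the group difference in change at the end of treatment. The other is a difference averaged over a period that, on the most natural reading, runs two weeks beyond treatment. An analysis plan that follows the Statistical analyses section faithfully would not test the hypothesis as worded.

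Two things are at stake. The primary estimate would depend partly on how quickly any effect fades once kava stops, which is not the question asked. And two defensible primary results would exist, a week-16 difference and a whole-period average, which could disagree on whether the trial succeeded.

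**Working it through.** **1. The texts side by side.** The hypothesis points to week 16. The analysis covers the entire study period. The outcome section, the stated trial length and the compliance section all run to week 18, whereas randomised treatment lasts 16 weeks. No sentence limits the primary contrast to week 16 or to weeks 2–16. This mismatch needs no arithmetic; the steps below only size it.

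**2. Reproducing the sample size.** For two equal groups, d = 2f = 0.30. For a between-group difference averaged over m visits, with equal correlation ρ between visits:

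v = (1 + (m − 1)ρ)/m; λ = (N/4)·δ²/v; power from the noncentral F on 1 and N − 2 df.

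With m = 6, ρ = 0.5 (assumed) and N = 206: v = 3.5/6 = 0.583, λ = 51.5 × 0.09/0.583 = 7.95, critical F = 3.887, power 80.1%. The smallest N reaching 80% is 206, as stated. ρ = 0.4 gives 178 and ρ = 0.6 gives 236; the group-by-time interaction at ρ = 0.5 gives 50. So the sizing targets an average over visits. Six of the seven scheduled visits could be weeks 0–16 or weeks 2–18; the text does not say which.

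**3. Effect of week 18 on an unadjusted, equal-weight average.** Assumptions: N = 210, ρ = 0.5, d = 0.30 at each of weeks 2, 4, 8, 12 and 16, no dropout.

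| Visits averaged | Share of effect left at week 18 | Average δ | Power |
|---|---|---|---|
| Weeks 2–18 (6) | all | 0.300 | 80.9% |
| Weeks 2–18 (6) | half | (5 × 0.30 + 0.15)/6 = 0.275 | 73.8% |
| Weeks 2–18 (6) | none | (5 × 0.30)/6 = 0.250 | 65.6% |
| Weeks 2–16 (5) | not used | 0.300 | 79.8% |

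In the third row λ = 52.5 × 0.0625/0.583 = 5.63, and 80% power would need N = 296. In the last row v = 3/5 = 0.60 and λ = 52.5 × 0.09/0.60 = 7.88. Over ρ = 0.3 to 0.7, the third row runs from 79.8% down to 54.9% and the last from 90.4% down to 69.9%.

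**4. The same comparison with baseline adjustment.** Adjustment replaces v by v − ρ²: 0.583 − 0.25 = 0.333 for six visits and 0.60 − 0.25 = 0.35 for five. With nothing left at week 18, dropping that visit changes power as follows:

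- constant effect: 88% to 96%;
- effect at weeks 2 and 4 equal to 0.25 and 0.5 of a plateau reached at week 8: 65% to 78%;
- linear rise to week 16 (0.125, 0.25, 0.5, 0.75, 1): 37% to 48%.

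**5. The week-16 contrast named in the hypothesis.** With baseline adjustment, v = 1 − ρ² = 0.75, λ = 52.5 × 0.09/0.75 = 6.30 and power is 70.5% (62.1% to 85.8% over ρ = 0.3 to 0.7); 80% needs N = 264. As a simple change score, v = 2(1 − ρ) = 1, power is 58.1%, and 80% needs N = 352.

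**The case against.** The strongest reply is that averaging over visits is a legitimate target, that the power calculation was built for it, and that it can be the more powerful choice. This is right. With baseline adjustment and a constant effect, the six-visit average has 88% power even with nothing left at week 18, against 70% for week 16 alone. With the plateau profile it is 65% against 70%. Averaging is therefore not the fault; the fault is that it is not the hypothesis and that the period averaged is not confined to treatment. It can also be said that a period called post-study lies outside the study period. That is possible, but the same sentence counts it in the trial length and the outcome section runs to week 18. Even with week 18 excluded, an average over weeks 2–16 is not the change at week 16.

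Several stronger readings are tempting but not supported:

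- **A much larger loss.** A reader might average all seven visits with baseline as a response, recovering 5/7 = 71% of a constant effect with about 53% power, and set that against 70%. The article gives no visit weights or baseline handling, and its power calculation uses six time points. The comparison also mixes unadjusted with adjusted: unadjusted week 16 has 58%.
- **Bias toward zero.** The average is a different estimand, not a biased estimate of itself.
- **Compromised rating at week 18.** Single-blind does not show that raters learn the randomised arm. The article does not say who is unblinded, and it keeps clinicians blind to treatment coding.
- **A plain contradiction on tablet duration.** Sixteen weeks of randomised treatment plus two weeks of placebo largely explains 18 weeks of tablets. The wording is unclear, and that is all that can be said.

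**Conclusion.** The point holds as a mismatch between the primary hypothesis and the primary contrast, together with an unresolved place for week 18. The mismatch is textual and does not depend on any power assumption.

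Its size does. Week 18 is one of six post-baseline visits, so in an equal-weight average it removes at most one sixth of a constant effect. The loss is nil if the effect fully persists, and exceeds one sixth only if the group difference reverses. The drop from about 80% to about 66% power rests on d = 0.30, ρ = 0.5, N = 210, complete data and no effect left at week 18. How fast the effect builds matters as much as how fast it fades: under a linear rise, the weeks 2–16 average is only 0.30 × 2.625/5 = 0.158.

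**What to change.** 1. Exclude week 18 from the primary contrast and analyse it separately as the post-treatment observation.
2. Name one primary contrast and make the hypothesis agree with it. Either use the MMRM difference in change from baseline at week 16, with the weeks 2–16 average as supportive, or use the weeks 2–16 average and reword the hypothesis to match.
3. Align the Primary outcome measure section with that choice.
4. In the Power analysis, state which six time points and what correlation were used, and restate power for the chosen contrast. At N = 210 and ρ = 0.5 this is about 70% for a baseline-adjusted week-16 contrast. For an unadjusted weeks 2–16 average with a constant effect it is about 80%, higher with baseline adjustment and lower if the effect builds slowly.
5. Reconcile the treatment and compliance sections on what is taken in weeks 16–18.

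The cost is wording and one recalculation, with no new visits or data. The real downside is that the stated 80% may become less favourable: a baseline-adjusted week-16 contrast would need 264 participants for 80% under these assumptions.
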